### Study endpoints

(1) Primary end point: Recurrence of Aspergillus infection. (2) Secondary end point: days of antifungal treatment. (3) Safety evaluation index: side effects of antifungal treatment.

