## Methods

### Study design and setting

The study was a single-center, prospective, non-blind, randomized, 24-month parallel controlled trial. The data of patients diagnosed with aspergilloma and surgically excision from Shanghai Pulmonary Hospital from January 1, 2020 to December 31, 2022 will be collected. After providing informed consent, enrolled patients will be randomly assigned for study group or the control group at a ratio of 1:1 using the block randomization method. Each patient will then receive a numeric randomization code. According to the literature and the results of the preliminary experiment, the recurrence rate of the experimental group is expected to be less than 1%, and that of the control group is about 20%. According to the ɑ value of 0.05 and the degree of certainty of 0.8, the sample content of each group is estimated by PASS 15 software to be 37 people, with the amplification of 1.1 times, and 40 patients are planned to be included in each group.

The study group will receive voriconazole orally for three months, twice a day, 0.2 g each time. The control group will not receive antifungal therapy. Detailed research process is described in Fig. 1.

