### Information recorded during follow-up

General condition, quality of life score [St. George’s Respiratory Questionnaire (SGRQ) score], lung function, sputum culture, G and GM test of peripheral blood, chest CT, immune status, etc. were recorded in baseline. Quality of life score, sputum fungal culture, G and GM test of peripheral blood, chest CT, and immune status were interviewed every three months. Checklist for clinical data collection and follow-up plan of enrolled patients is showed in Table 1.

**Table 1 Tab1:** Checklist for clinical data collection and follow-up plan of enrolled patients

	Screening stage	Treatment period (one day to three months after enrollment)	Evaluation period (once every three months for 24 months)
Informed consent	X		
Demographic statistics	X		
History of present illness and treatment	X		
Symptoms and vital signs	X	X	X
Inclusion/exclusion criteria	X		
Blood routine	X	X	X
Blood biochemical test	X	X	X
G test of peripheral blood	X	X	X
GM test peripheral blood	X	X	X
CD4/CD8	X	X	X
IgA, IgG, IgM	X	X	X
HCG of peripheral blood or urine	X		
Noninvasive oxygen saturation	X		
Chest CT	X	X	X
Electrocardiograph	X	X	X
Fungal smear and culture	X	X	X
Basic drugs and combined drugs	X	X	X
Distribution of research drugs	X		
Recall of research drug		X	X
Evaluation of adverse events	X	X	X
Schedule of next visit		X	X
Compliance evaluation		X	X
effectiveness evaluation		X	X
SGRQ score	X	X	X
Evaluation of microbiological efficacy		X	X
Survival		X	X

HCG, human chorionic gonadotropin; Ig immune globulin; SGRQ, St. George’s Respiratory Questionnaire

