### Safety indicators

Including recurrence of aspergillus infection and adverse reactions such as liver and kidney function damage and etc.

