In general, more evidence-based medical evidence is needed to explore whether antifungal agents should be used after aspergilloma surgery, the appropriate course of treatment and the safety of drugs. There are both advantages and disadvantages of antifungal therapy. The disadvantages are the high expense of antifungal drugs, the heavy economic burden on patients, and the high risk of liver and kidney function damage caused by antifungal drugs. The advantage of antifungal therapy is that it may reduce the risk of aspergillus recurrence. The advantage of non-antifungal therapy is to reduce the overtreatment in some cases and reduce the economic burden of patients. But its disadvantage is that the risk of fungal infection recurrence may be increased. Therefore, more clinical studies are needed to provide evidence-based medical evidence for the following issues: (1) Further analysis is needed to determine whether anti-fungal treatment after aspergilloma bulbectomy has an impact on recurrence of aspergillus infection. (2) Duration and safety of antifungal therapy.

This study was designed to evaluate the difference in recurrence risk and safety of antifungal agents in patients with pathologically confirmed aspergilloma after surgery in a single-center, randomized, parallel grouping, prospective, 2-year clinical study. Through regular supervision record of aspergilloma recurrence, the quality of life, lung function and safety evaluation of fungi treatment, to explore the most suitable treatment for aspergilloma, to improve the quality of life of patients with more advantages, reduce the recurrence of aspergillus infection, improve the prognosis of patients with aspergilloma eventually. The study results will provide high-quality evidence-based medical evidence for the formulation, revision and optimization of international and domestic clinical guidelines and expert consensus on chronic aspergillus lung disease, effectively improve the clinical treatment effect, and form the latest concept of diagnosis and treatment of aspergilloma.

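### In a non-blind trial with an untreated control, nothing in the article keeps the call of the primary endpoint, recurrence, masked to allocation

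*Protocol article*

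**What the plan says.** - **Blinding and control.** Protocol article, Study design and setting: "The study was a single-center, prospective, non-blind, randomized, 24-month parallel controlled trial". The same section says of the comparator: "The control group will not receive antifungal therapy". No placebo is mentioned.
- **Endpoint.** Study endpoints: "Primary end point: Recurrence of Aspergillus infection". The entry names no assessor and no masking, and neither appears elsewhere in the article.
- **Data from which an event would be called.** Information recorded during follow-up: "Quality of life score, sputum fungal culture, G and GM test of peripheral blood, chest CT, and immune status were interviewed every three months". Table 1 repeats these items at each evaluation visit.
- **Second role.** Study endpoints gives side effects of treatment as the only safety index. The Safety indicators section nevertheless reads: "Including recurrence of aspergillus infection and adverse reactions such as liver and kidney function damage and etc".
- **Other names.** The Discussion speaks of aspergilloma recurrence ("Through regular supervision record of aspergilloma recurrence") and of fungal infection ("But its disadvantage is that the risk of fungal infection recurrence may be increased"). The title, Abstract, Background, Study endpoints, Statistical analysis and Safety indicators all refer to aspergillus infection.

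**The concern.** Everyone who sees the patient knows whether voriconazole was given. Culture and G/GM results are partly objective, but someone must read the CT and decide whether a set of findings amounts to recurrence. If that person knows the arm, the same findings may be called an event more readily in an untreated patient. Randomization does not protect against this, because the bias arises after allocation.

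The trial is small: 40 per group, with about 40 × 0.20 = 8 control events and 40 × 0.01 = 0.4 study-arm events expected under the planned effect. A few differently called cases can therefore move the error rate. The risk is a false claim that antifungal treatment prevents recurrence.

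**Working it through.** **Inputs from the article (Study design and setting; Statistical analysis).** Expected recurrence is below 1% with treatment (0.01 used) and about 20% without. Alpha is 0.05 and power 0.80. The calculated size is 37 per group, with 40 planned. Allocation is 1:1, and recurrence is analysed by a Cox model. A two-sided test is assumed, since the article does not state sidedness.

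**Inputs assumed.** The article gives no over-calling rate, so 5% and 10% of recurrence-free controls are used. For no drug effect, the true rate is taken as the same in both arms: 20% (the article's untreated rate), 10% and 5%.

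**Step 1: reproduce the plan's figure.** Unpooled normal formula:

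n = (1.960 + 0.842)² × (0.20×0.80 + 0.01×0.99) / (0.20 − 0.01)² = 7.849 × 0.1699 / 0.0361 = 36.94, so 37 per group.

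This matches. The inflation gives 37 × 1.1 = 40.7, against 40 planned. The sample size is not in dispute.

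**Step 2: observed control rate under over-calling.** With true rate p and over-call fraction f, the called rate is p + f(1 − p) in controls and p in the study arm. The number of extra control calls is 40 × f(1 − p).

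- p = 20%: f = 5% gives 24% (1.6 extra calls); f = 10% gives 28% (3.2).
- p = 10%: 14.5% (1.8) and 19% (3.6).
- p = 5%: 9.75% (1.9) and 14.5% (3.8).

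**Step 3: false-positive rate.** For the chi-square (uncorrected) and Fisher tests, the binomial probabilities of every pair of event counts significant at two-sided 0.05 were summed exactly. The log-rank column stands in for the planned Cox analysis: 8 quarterly visits, constant hazard, 20,000 simulated trials.

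| True rate, both arms | Over-call of controls | Chi-square | Log-rank | Fisher |
|---|---|---|---|---|
| 20% | none | 5.1% | 4.7% | 2.8% |
| 20% | 5% | 7.2% | 6.8% | 4.3% |
| 20% | 10% | 13.3% | 12.9% | 8.8% |
| 10% | none | 5.9% | 5.2% | 1.7% |
| 10% | 5% | 10.1% | 9.6% | 4.7% |
| 10% | 10% | 21.4% | 20.9% | 13.5% |
| 5% | none | 4.3% | 3.9% | 0.4% |
| 5% | 5% | 13.8% | 12.8% | 3.9% |
| 5% | 10% | 32.6% | 30.7% | 16.4% |

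Under over-calling, most of the false positives favour voriconazole. At 20% and a 10% over-call, 13.0 of the 13.3 percentage points (chi-square) do so.

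**The case against.** **The article does not say that an investigator judges recurrence.** A reader might infer this from the open design, but the article is silent on the assessor, and several of the scheduled tests are partly objective. What stands is that nothing shown keeps the call masked.

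**This is a condensed article.** A recurrence criterion and reading procedures are commonly left to the full protocol, so their absence here is not an error. That is right, and the point does not rest on a missing definition. It rests on the stated open design with an untreated control, and on a cheap protection that the article does not mention.

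**The naming is mostly consistent.** Aspergilloma recurrence and fungal infection recurrence are loose Discussion wording. The microbiological efficacy row in Table 1 is a separate assessment; a reader might take it for another name of the endpoint, but nothing presents it so. The firmer textual conflict is recurrence as both primary endpoint and safety indicator.

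**A handful of calls need not decide the trial.** One might reason that with about 8 events in total, one to four extra calls settle the result. But 8 is the count under the planned effect, where a split of about 8 v 0 is already significant (4 v 0 suffices: chi-square 4.21, p = 0.040). With no effect and 8 events split 4 v 4, four extra control calls give 8 v 4, p = 0.21. From 5 v 3 they give 9 v 3, p = 0.06. The risk is a raised error rate, not a result decided by a few calls.

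**The inflation depends on the test and the assumptions.** With Fisher's test a 5% over-call keeps the error below 5%. However, the article plans a Cox model for recurrence and mentions Fisher's test only for baseline data. The log-rank figures are close to the chi-square ones.

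**Conclusion.** The concern holds as a design weakness that is cheap to reduce, not as a demonstrated bias. With an open, untreated control, the article does not say who calls recurrence or that the call is masked.

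At the protocol's own 20% rate the inflation is modest for a 5% over-call and clear for a 10% over-call (about 13% by chi-square or log-rank). It is larger if true recurrence is lower: up to about 31% to 33% at a true rate of 5% with a 10% over-call. With Fisher's test the corresponding ranges are about 4% to 5% and 9% to 16%.

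These figures rest on assumed over-calling, in controls only, and on the same true rate in both arms. The article supports neither the presence nor the size of such over-calling.

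**What to change.** 1. Have the radiologists and laboratory staff who already handle the scheduled CT, culture and G/GM tests read them without the allocation on the request.
2. Make the recurrence call from those masked readings by one criterion, chosen by the investigators, fixed in advance and applied identically in both arms. Which findings should count is a clinical decision for the investigators; the article gives no basis for a reviewer to set it.
3. Use recurrence of Aspergillus infection as the only endpoint name, and reconcile Study endpoints with Safety indicators on its role.

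The cost is one protocol paragraph and a change to the request forms. No placebo, extra visit or extra reader is needed. Trial status reports 8 patients enrolled, so nearly all of the planned 80 could still be assessed this way. The downside is that masking is imperfect if clinicians discuss treatment with the readers.

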### Clinical data to be collected

Basic information:(a) Name, sex and age. (b) Living and working environment. (c) complications.Treatment after aspergilloma resection:(a) Preoperative serological indexes of aspergillus infection: 1,3-β -D glucan detection (G test) and galactose mannitolglycan antigen detection (GM test). (b) Serological indexes of postoperative aspergillus infection: G test and GM test. (c) Preoperative blood routine biochemical indexes: liver function, kidney function and electrolyte. (d) Postoperative biochemical indexes: liver function, kidney function and electrolyte. (e) Preoperative immune indicators: CD4, CD8, CD4/CD8, immune globulin (Ig) A, IgG, IgM in peripheral blood. (f) Postoperative immune indicators: CD4, CD8, CD4/CD, IgA, IgG, IgM in peripheral blood. (g) Whether it is antifungal therapy, antifungal drug, dose and course of treatment. (h) Chest computerized tomography (CT). (i) The time and results of fungal smear and culture of lower respiratory tract specimens.

### Research indicators

(1) Laboratory examination. (2) Imaging examination. (3) Surgical method. (4) Treatment.

### Prognosis assessment

Telephone and outpatient follow-up.

### Information recorded during follow-up

General condition, quality of life score [St. George’s Respiratory Questionnaire (SGRQ) score], lung function, sputum culture, G and GM test of peripheral blood, chest CT, immune status, etc. were recorded in baseline. Quality of life score, sputum fungal culture, G and GM test of peripheral blood, chest CT, and immune status were interviewed every three months. Checklist for clinical data collection and follow-up plan of enrolled patients is showed in Table 1.

**Table 1 Tab1:** Checklist for clinical data collection and follow-up plan of enrolled patients

	Screening stage	Treatment period (one day to three months after enrollment)	Evaluation period (once every three months for 24 months)
Informed consent	X		
Demographic statistics	X		
History of present illness and treatment	X		
Symptoms and vital signs	X	X	X
Inclusion/exclusion criteria	X		
Blood routine	X	X	X
Blood biochemical test	X	X	X
G test of peripheral blood	X	X	X
GM test peripheral blood	X	X	X
CD4/CD8	X	X	X
IgA, IgG, IgM	X	X	X
HCG of peripheral blood or urine	X		
Noninvasive oxygen saturation	X		
Chest CT	X	X	X
Electrocardiograph	X	X	X
Fungal smear and culture	X	X	X
Basic drugs and combined drugs	X	X	X
Distribution of research drugs	X		
Recall of research drug		X	X
Evaluation of adverse events	X	X	X
Schedule of next visit		X	X
Compliance evaluation		X	X
effectiveness evaluation		X	X
SGRQ score	X	X	X
Evaluation of microbiological efficacy		X	X
Survival		X	X

HCG, human chorionic gonadotropin; Ig immune globulin; SGRQ, St. George’s Respiratory Questionnaire

### Statistical analysis

Double entry of data was performed with Epidata 3.1 software, and data analysis was performed with SAS 9.4 (SAS Institute, Cary, North Carolina) statistical software. Before the analysis, normality test was carried out, and the normalized data were consistent with normality. Mean ± standard deviation was used for continuous variables, and percentage was used for classified variables. The baseline data were analyzed by T test or Fisher’s exact probability, chi-square test, etc. Cox proportional risk regression model was used to analyze the influencing factors of antifungal therapy on aspergillus infection recurrence after aspergillus bulbectomy. Cox multiple regression model was used for optimal model fitting, and regression coefficient (β), relative risk (RR) and 95% confidence interval (CI) of RR were calculated.

### Safety indicators

Including recurrence of aspergillus infection and adverse reactions such as liver and kidney function damage and etc.

### Risk control

The risk of patients participating in this study comes from the risk of the disease itself. Theoretically, the study itself does not increase the risk of disease in patients. Patients may still discontinue treatment or withdraw from the study at any time, and subjects may discontinue the study at any time or for any reason at their own request or at the request of the Investigator. For all subjects who withdraw from the study for any reason, contact them or their family or healthcare provider 24 weeks after withdrawal to determine the subject’s life status. Subjects may voluntarily discontinue treatment at any time without affecting further treatment.

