### Exit criteria

Withdrawal decided by the researcher:(a) Refers to the decision of the investigator to withdraw an enrolled subject from the study if it is not suitable to continue the study during the study. (b) Subjects have poor compliance with the protocol. (c) Severe adverse events or intolerable adverse events occur during the study. (d) The subject has some comorbidities, complications or special physiological changes and is not suitable for further study. (e) Other circumstances in which the investigator determines the need to withdraw from the study.Subjects voluntarily withdraw from the study:(a) The subject is unwilling to continue the clinical trial and proposes withdrawal to the investigator. (b) lost to follow-up. (c) Subjects who withdraw early shall indicate the reasons for withdrawal on the case report form. Patients who withdraw due to adverse events should be followed up until the adverse events disappear or have a clear explanation.

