The selection of individual subjects violates the inclusion/exclusion criteria and should not be included in the test;During the study period, the researcher considers that the subject has other factors that can not continue to participate in the study, and actually discontinues the subject’s continued participation in the study;During the test, the subjects do not comply with the test plan and the compliance is poor. For example, the samples for effectiveness and safety evaluation cannot be collected as required by the test plan, and there is no data, etc.The Investigator has the right to discontinue the subject’s participation in the study if: the investigator must carefully evaluate the discontinued subject, take active treatment, and record this procedure in detail in the original notebook. If a subject withdraws from the study due to an adverse event, abnormal laboratory test values, or test failure, he or she must also be assessed and treated accordingly, and this procedure must be documented in detail in the original notebook. The investigator may also determine at any time during the study whether or not the subject should continue the clinical trial based on medical judgment.Termination test standard:Termination of a trial is when the trial has not completed the evaluation of all subjects as planned. After cessation of the study, new subjects will not be included, and those enrolled but not yet out of the study will be examined and interviewed in accordance with the investigator’s consultation. If the study is found to have no clinical value during the trial, the trial should be terminated;(a) Major errors in the clinical trial protocol were found during the trial, making it difficult to evaluate the effect of the study. (b) If serious deviations occur in the implementation of the test, the test should be stopped if it is difficult to evaluate the effect of the study if it continues. (c) Termination at the request of the investigator (for reasons of funding, management, etc.). (d) The China Food and Drug Administration orders the termination of the trial for some reason. (e) The ethics committee shall terminate the trial from the perspective of protecting the rights and interests of the subjects.

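### Patients withdrawn from the study for poor compliance or adverse events are no longer assessed for recurrence, and this loss of the primary endpoint is likely to be unequal between arms and informative

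*Protocol article*

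**What the plan says.** The primary endpoint is recurrence of Aspergillus infection (Study endpoints). CT, G and GM tests and fungal culture are scheduled every three months to month 24 (Information recorded during follow-up, Table 1). The trial is open label. The study group takes voriconazole for three months and the control group takes no antifungal drug (Study design and setting).

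Under Exit criteria, the grounds on which the investigator may withdraw a patient from the study include:
- "Subjects have poor compliance with the protocol";
- "Severe adverse events or intolerable adverse events occur during the study".

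After exit the protocol provides three things:
- an early exit interview (end of Elimination criteria);
- for adverse-event withdrawals, follow-up of the event until it is resolved or explained (Exit criteria);
- for everyone who leaves, whatever the reason, an instruction to "contact them or their family or healthcare provider 24 weeks after withdrawal", with life status as its stated purpose (Risk control).

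The analysis is a Cox model for recurrence (Statistical analysis).

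**The concern.** A patient who leaves after an adverse event or for poor compliance has no planned recurrence assessment after the exit interview. Voriconazole is taken in the first three months, so an exit for a drug-related reason leaves roughly 24 − 3 = 21 months or more unassessed.

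Two features make this more than a loss of precision. First, controls take no study drug, so drug intolerance and drug non-adherence can occur only in the voriconazole arm. The Discussion itself names liver and kidney damage as a considerable risk of antifungal drugs. Second, patients who leave for these reasons have had the least drug. Under the trial's own hypothesis their later risk should lie nearer the control risk than that of patients who completed treatment. A Cox model that censors them at exit assumes their later risk equals that of comparable patients still followed. If it is higher, the voriconazole arm looks better than it is. Recurrences that nobody looked for cannot be put back by the analysis; they can only be assumed in sensitivity analyses.

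**Working it through.** **Inputs from the protocol (Study design and setting).** Recurrence about 20% in controls and below 1% with voriconazole (0.01 used); alpha 0.05; "the degree of certainty of 0.8", read as power; 37 per arm, enlarged by 1.1, with 40 per arm planned.

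**Assumptions, not in the protocol.** Share of the voriconazole arm that leaves: 10–20%. Recurrence risk q in those patients: from 1% (same as those who stay) to 20% (same as controls). Control loss is set to zero to isolate the effect.

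**Step 1: the plan's own figure.** Two proportions, unpooled variance, two-sided:

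n = (1.960 + 0.842)² × (0.20 × 0.80 + 0.01 × 0.99) / (0.20 − 0.01)² = 36.94, rounded up to 37.

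This matches the protocol. 37 × 1.1 = 40.7, against 40 planned. Going from 37 to 40 covers a loss of 1 − 37/40 = 7.5%.

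**Step 2: true rate in the voriconazole arm when some patients are not assessed.**

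True rate = (number staying × 0.01 + number leaving × q) / 40.

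| Leave | Stay | q | True rate | True difference from 20% | Expected unseen recurrences |
|---|---|---|---|---|---|
| 4 (10%) | 36 | 0.20 | (0.36 + 0.80)/40 = 2.9% | 17.1 points | 0.8 |
| 8 (20%) | 32 | 0.20 | (0.32 + 1.60)/40 = 4.8% | 15.2 points | 1.6 |
| 4 or 8 | 36 or 32 | 0.01 | 1.0% | 19.0 points | 0.04 or 0.08 |

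The observed rate is 1% in every row, because it comes only from those who stay. The apparent difference is therefore 19 points throughout. The bias is 1.9 to 3.8 points at q = 20% and zero at q = 1%. These are simple proportions with exit early in follow-up; they show the size of the problem and are not a model of the Cox estimate.

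**Step 3: fragility.** The design expects 0.20 × 40 = 8 control events and 0.01 × 40 = 0.4 voriconazole events, that is 0 or 1. Two-sided Fisher tests against 8/40:

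| Voriconazole events | p |
|---|---|
| 0/40 | 0.0053 |
| 1/40 | 0.029 |
| 2/40 | 0.087 |

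Significance at 0.05 is lost at the second voriconazole event. If one recurrence has been seen, one unseen recurrence is enough; if none has been seen, it takes two.

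**Step 4: how likely are two or more unseen recurrences?** With q = 20%:
- 4 patients leave: 1 − 0.8⁴ − 4 × 0.2 × 0.8³ = 1 − 0.4096 − 0.4096 = 18%.
- 8 patients leave: 1 − 0.8⁸ − 8 × 0.2 × 0.8⁷ = 1 − 0.168 − 0.336 = 50%.

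**Step 5: power.** With the pooled normal approximation, 40 versus 40 gives 0.803. Loss in the voriconazole arm alone gives 0.774 at 36 versus 40 and 0.736 at 32 versus 40. The loss of power is modest; possible bias is the larger issue.

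**The case against.** Several stronger readings are tempting, and the document does not support them.

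- *A reader might infer that the endpoint is lost only in the voriconazole arm.* The exit ground is compliance with the protocol, not with the drug. The example under Elimination criteria is samples that cannot be collected, which can happen in either arm. Adverse events are not limited to drug events, and every patient has had surgery. Comorbidity, voluntary withdrawal and loss to follow-up apply to both arms, and no withdrawal rates are given. What stands is that one source of exits exists in one arm only, so inequality is likely but not certain.
- *A reader might infer that a withdrawn patient gets one call and nothing else.* There is also the exit interview and the adverse-event follow-up. Neither is a recurrence assessment to month 24.
- *A reader might infer that the plan equates stopping drug with leaving the study.* Risk control names the two as alternatives, and nothing says that a patient who merely stops voriconazole loses the three-monthly visits. The defect lies in the exits decided by the investigator.
- *A reader might take failure as a further informative reason for exit*, from "If a subject withdraws from the study due to an adverse event, abnormal laboratory test values, or test failure" under Elimination criteria. The term is undefined. If it means recurrence, the endpoint has already been seen, and at 20% versus below 1% such exits would fall mainly in the control arm.
- *A reader might conclude that two unseen events decide the trial*, by letting 2 of 4 withdrawn patients recur: 0/36 versus 8/40 (p = 0.0057) becomes 2/40 versus 8/40 (p = 0.087). That is a 50% risk, 2.5 times the planned control rate, and it is an unfavourable scenario. At 20%, two or more of four recur about 18% of the time.

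Finally, the article condenses a fuller protocol that may say more. This defence is limited, because Risk control states the contact after withdrawal, its timing and its purpose. The point concerns a stated rule and not a missing detail.

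**Conclusion.** The concern holds in this form: followed as written, the plan stops assessing recurrence in patients whom the investigator withdraws for poor compliance or adverse events, and the loss is likely to be unequal between arms and informative. If 10–20% of the voriconazole arm leaves and recurs at 20%, the true arm rate is 2.9–4.8% instead of the observed 1%, and the difference is overstated by 1.9 to 3.8 points. If those patients recur at 1%, there is no bias. The loss rate and their risk are both assumptions, and any informative loss among controls is not counted. The bias is moderate on this range, but with 0 or 1 expected voriconazole events against 8, one or two unseen recurrences could change the conclusion. That, and the fact that unassessed outcomes cannot be recovered later, makes it worth correcting while the trial is recruiting. Trial status reports 8 of the planned 80 patients enrolled.

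**What to change.** Amend Exit criteria and Risk control as follows.

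1. Separate stopping study drug from leaving the study. Poor compliance and adverse events should not by themselves end outcome follow-up.
2. Keep patients withdrawn on these grounds, in either arm, on the existing three-monthly recurrence assessments (CT, G and GM tests, fungal culture) to month 24, unless they withdraw consent for follow-up.
3. For those who do leave, record recurrence and antifungal use as well as life status at the 24-week contact.

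The criteria for stopping the drug are left unchanged.

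The cost is a protocol amendment and slightly more follow-up effort. The visits are of a type already in Table 1 and the sample size does not change. The document gives no budget, so the cost of keeping these patients in follow-up cannot be judged from it.

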### Elimination criteria

Prior to statistical analysis of the data, the main researcher, the sponsor and the statistical unit shall judge whether to exclude the individual cases. If one of the following situations occurs, the principal investigator shall comprehensively judge whether to exclude the subject based on the degree of completion of the test and the reasons for withdrawal, and make relevant explanations:

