For all subjects who terminate the study early, the investigator should obtain, as far as possible, the reason for withdrawal from the study, such as adverse events, ineffectiveness of corrective actions, withdrawal based on the investigator’s decision, or other reasons, and the reason for withdrawal should be recorded in the case report form (CRF). Subjects who quit early should complete the early exit interview according to the schedule of the visit procedure.

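### Patients can be withdrawn from the study for non-compliance or adverse events, and recurrence, the primary end point, is not assessed after exit; missed events can therefore differ by arm

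*Protocol article*

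**What the plan says.** The trial is non-blind. One arm is assigned voriconazole for three months and the other no antifungal (Study design and setting). The primary end point is recurrence of Aspergillus infection (Study endpoints), and Table 1 schedules evaluation every three months for 24 months.

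**Leaving the study.** Among the investigator's grounds for withdrawal, Exit criteria lists "Subjects have poor compliance with the protocol" and "Severe adverse events or intolerable adverse events occur during the study".

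**After exit.** Three things are fixed:
- Elimination criteria: "Subjects who quit early should complete the early exit interview according to the schedule of the visit procedure". The same section requires that discontinued subjects be evaluated, and treated where needed.
- Exit criteria: "Patients who withdraw due to adverse events should be followed up until the adverse events disappear or have a clear explanation".
- Risk control, for withdrawal of any kind: "contact them or their family or healthcare provider 24 weeks after withdrawal to determine the subject’s life status".

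**Before analysis.** Under Elimination criteria, "the main researcher, the sponsor and the statistical unit shall judge whether to exclude the individual cases". The principal investigator weighs how much of the trial was completed and why the patient left. One listed ground is "During the test, the subjects do not comply with the test plan and the compliance is poor"; another is discontinuation by the researcher.

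**The concern.** The exit rules end participation in the study, while the provisions after exit track the adverse event and survival. A recurrence already present at exit can be recorded at the exit interview. One that appears later has no planned CT, culture or serology to detect it.

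This matters more than ordinary drop-out because the grounds for exit are tied to treatment. The Discussion itself refers to "the high risk of liver and kidney function damage caused by antifungal drugs", and only one arm is assigned such a drug. A patient withdrawn for toxicity in month 1 has had a shortened course and may go up to 23 months without a planned recurrence assessment. The Cox model would have to censor or omit such patients, which assumes that their leaving is unrelated to recurrence. Very few events are expected, so a handful of unseen ones can count.

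The elimination rule is a secondary concern. It lets knowledge gained after randomisation, in an open trial, decide who is analysed.

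**Working it through.** **Inputs from the protocol (Study design and setting).** Recurrence 1% on voriconazole (stated as below 1%) and 20% in controls; alpha 0.05, taken as two-sided; power 0.80; 37 per arm, multiplied by 1.1 and planned as 40.

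**The plan's own figure.** Unpooled two-proportion formula: (1.960 + 0.842)² × (0.01×0.99 + 0.20×0.80) / 0.19² = 36.94, so 37 per arm. This reproduces. 37 × 1.1 = 40.7, planned as 40, which leaves 3 spare patients per arm.

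**Expected events.** Controls: 40 × 0.20 = 8. Voriconazole: 40 × 0.01 = 0.4.

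**Assumption.** The document gives no withdrawal rate. Three per arm is used below because it equals the spare patients.

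**1. Removal unrelated to outcome.** Exact enumeration of the pooled z test, counting significance in favour of voriconazole: 40 per arm gives power 0.909; 37 per arm gives 0.882. The cost is small.

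**2. Voriconazole patients withdrawn, later recurrence unseen.** Three of 40 leave and 37 remain.
- Counted events: 37 × 0.01 = 0.37, a rate of 1%. Counted risk ratio: 0.01 / 0.20 = 0.05.
- Missed events: 3 × r, where r is the later recurrence risk of those who left (assumed).
- True rate: (0.37 + 3r) / 40. True ratio: that rate / 0.20.

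| r | Missed events | True rate | True risk ratio |
|---|---|---|---|
| 5% | 0.15 | 1.30% | 0.065 |
| 10% | 0.30 | 1.68% | 0.084 |
| 20% | 0.60 | 2.43% | 0.12 |

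**3. Sensitivity of the conclusion to single events.** Two-sided Fisher p for 8/40 controls against 0, 1, 2 and 3 of 40 on voriconazole: 0.005, 0.029, 0.087 and 0.193. From a counted 0 of 40, two missed recurrences move the result across 0.05; from a counted 1 of 40, one does.

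**4. Worst-case illustration in the other direction.** Suppose k controls are removed before a recurrence that is then never counted. Exact pooled-z power falls from 0.909 to 0.834, 0.729 and 0.597 for k = 1, 2, 3. It is the same to within 0.001 whether those patients are eliminated or kept as event-free. A log-rank simulation (20,000 runs, exponential times, events found at three-monthly visits) agrees: 0.896 at base, 0.880 with three per arm censored at random, and 0.834, 0.730 and 0.595 for k = 1, 2, 3.

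**The case against.** - **Analysis sets belong in a statistical analysis plan, which is not shown.** This is fair as to elimination. A reader might infer that the primary Cox analysis will drop non-compliers, but the document does not say so; it permits case-by-case exclusion without naming an analysis set. The objection does not reach post-exit follow-up, because no analysis plan can supply assessments that were never made.
- **Adverse events are not a listed ground for elimination.** Correct. They enter only indirectly, through the reason for withdrawal or through discontinuation by the researcher. Poor compliance is explicit.
- **Risk control already distinguishes stopping treatment from leaving the study, and only severe or intolerable events are listed for exit.** This stands. A patient who stops voriconazole for a mild liver-test change need not exit. The Discussion's remark on toxicity is general and is not a withdrawal rate for this trial. Non-compliance and severe events nevertheless remain grounds for leaving the study itself.
- **A condensed article may omit a fuller exit schedule.** Possibly: an early-exit visit is mentioned but has no column in Table 1. Yet Risk control does prescribe a contact for all withdrawals and names life status as its purpose.
- **The control-arm power losses are constructed.** They are. They need controls to be removed selectively before recurrence and every such event to be missed. One could imagine a control who starts an antifungal for suspected infection and is judged non-compliant; the text permits this but does not state it, and the exit interview might record the recurrence. A reader should not take power of 0.60 as a forecast.
- **The voriconazole route is modest.** Risk ratios of 0.05 and 0.12 both describe a very large benefit, and 1/40 against 8/40 is still significant.

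**Conclusion.** The point holds for follow-up after exit. The stated rules allow study withdrawal on grounds related to treatment and then fix no assessment of the primary end point to month 24, so recurrences can be missed to different degrees in the two arms. Discretionary elimination on post-randomisation facts is a secondary weakness.

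A reader might go further and infer that the result will be biased in favour of voriconazole. The document does not support that. Unseen recurrences in withdrawn voriconazole patients would overstate benefit; controls removed before recurrence would understate it and cost power. Frequencies are given for neither, so the size and net direction cannot be derived. The illustrations rest on the protocol's 1% and 20% rates and on assumed removals: little loss if removal is unrelated to outcome, a modest shift in the risk ratio for three voriconazole withdrawals, and a large power loss only in the worst case for controls. With about 8 and 0.4 expected events, the matter should be corrected, with medium confidence in its practical importance.

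**What to change.** In Exit criteria and Elimination criteria, state that non-compliance, an adverse event, stopping study drug or starting a non-assigned antifungal, in either arm, ends study drug where needed, but does not end follow-up and is not a ground for elimination from the primary analysis. Stopping voriconazole for safety remains the clinician's decision.

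Follow every randomised patient who has not withdrawn consent for recurrence on the existing three-monthly schedule to month 24. This should be in addition to the life-status contact in Risk control: replacing that contact would remove the only one fixed for all patients who withdraw consent. Analyse as randomised, and keep compliance-based exclusions for a secondary per-protocol analysis.

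**Cost.** A protocol amendment, probably with ethics review, since the trial is approved and recruiting. No added patients and no new visit types: with 3 withdrawals per arm, at most 6 × 8 = 48 of the 80 × 8 = 640 scheduled evaluation visits would be kept instead of lost. The drawbacks are continued contact with patients off their assigned treatment and some dilution of the effect by off-assignment antifungal use. Only 8 patients had been enrolled according to Trial status, so at that point a change would have covered nearly the whole trial.
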